#### Waiting list control group (WLCG)

The WLCG will not receive any treatment during the intervention phase but will take part in a three-week waiting period during which subjects will follow their usual daily routine. To reduce barriers to participation due to possible group preferences [40], the WLCG will attend a control group programme after their study completion. The programme consists of the same language course intervention as the LLG and an additional voluntary examination after the end of the course. This appointment is not included in the main study design as the scope for participation should differ as little as possible between groups.

### Outcomes

Baseline variables, as well as primary, secondary, and language course outcome measures are presented in Fig. 1. Unless otherwise stated, primary and secondary outcome measures are valid and reliable tests from the Vienna Test System (VTS) [34]. The VTS is a computerised test system for the assessment of neuropsychological functions and has become a well-established tool in clinical practice. Each cognitive outcome will begin with an instruction phase, followed by a practice phase, in which participants will receive immediate feedback on their errors. If necessary, the practice phase can be repeated to ensure a sufficient understanding of the task.

**Fig. 1 Fig1:**
[figure not shown]
SPIRIT figure for the schedule of enrolment, interventions, and assessments. P primary outcome measure, S secondary outcome measure, −t2 telephone screening, −t1 face-to-face screening, t1 pre-assessment, t2 language course/waiting period, t3 post-assessment, t4 3-month follow-up assessment, t5 language course, t6 4-month follow-up assessment (waiting list control group only). Abbreviations: CFD Cognitive Functions Dementia, CRIq Cognitive Reserve Index questionnaire, DSB Digit Span Backwards, DSF Digit Span Forwards, FLANDERS Flinders Handedness Survey, INHIB Response Inhibition, LLG Language learning group, LSBQ The Language and Social Background Questionnaire, NBV N-Back Verbal, STROOP Stroop Interference Test, SWITCH Task Switching, TMT-A/−B Trail-Making Test – Langensteinbach Version part A/part B, WAFA Perception and Attention Function Battery – Alertness, WAFG Perception and Attention Function Battery – Divided Attention, WIWO Vienna Verbal Fluency Test, WLCG Waiting list control group

#### Baseline variables

Baseline variables include socio-demographic variables such as date of birth, gender, marital and occupational status, as well as an assessment of global cognitive functions. Additionally, cognitive reserve, foreign language knowledge and usage, and handedness will be examined.

##### Cognitive reserve

We will evaluate cognitive reserve using the Cognitive Reserve Index questionnaire (CRIq) [41]. The CRIq is a valid and reliable half-structured interview, which quantifies cognitive reserve over an individual’s lifetime using three established measures of cognitive reserve: education (CRI-Education), occupation (CRI-WorkingActivity), and engagement in cognitively stimulating activities (CRI-LeisureTime) [42]. The three sub-scores can be combined into an overall score (CRI-Index). All measures are age-adjusted to allow for comparisons between different age groups.

##### Foreign language knowledge and usage

Foreign language knowledge and usage will be determined using the Language and Social Background Questionnaire (LSBQ) [43]. The LSBQ is a validated and reliable questionnaire for self-assessment of foreign language skills and usage in various contexts. A composite factor score quantifies the degree of bilingualism on a continuum from clearly monolingual to highly bilingual.

##### Global cognitive functions

We will assess global cognitive functioning using the Cognitive Functions Dementia test set (CFD, test form: S1 [touchscreen operation]) [34, 35] to exclude participants with suspected cognitive decline according to Petersen’s criteria (no subtest *z* ≤ − 1.5) [36].

The CFD is a comprehensive computer-based assessment from the VTS and takes about 60 min to perform. Previous studies in this field of research only used brief screening measures such as the Mini-Mental State Examination (MMSE) [44] or the Montreal Cognitive Assessment (MoCA) [45]. Both instruments can distinguish pathological cognitive decline from healthy ageing. However, they are less accurate than comprehensive multidimensional neuropsychological inventories [46]. In the CFD, cognitive performance is measured by eleven tasks falling into five cognitive domains: attention, verbal long-term memory, EF, expressive speech, and perceptual motor functions.

##### Handedness

The Flinders Handedness survey (FLANDERS) [47] is a short standardised questionnaire to measure hand preference. It contains ten items describing ten different activities (e.g. writing). Participants are asked to indicate whether they prefer the left, the right or either hand for each activity.

#### Primary outcomes

The Stroop Interference Test (STROOP, test form: S7) [48] and the Divided Attention, a subtest of the Perception and Attention Function Battery (WAFG, test form: S3) [49], are the two primary outcome measures.

##### Stroop Interference Test (STROOP)

The STROOP is a sensory-motor speed test that determines interference — a measure of inhibitory control. In a small pilot study older adults performed significantly better in this task after having participated in a foreign language training [24]. The task consists of two baseline and two interference conditions (see Fig. 2a). In the (i) reading baseline condition, participants read one of four German colour words (blue, green, red, yellow) printed in black one after the other on a computer screen. Similarly, in the (ii) naming baseline condition, subjects see coloured bars (blue, green, red, yellow). The task is to select the corresponding colour on the response panel as quickly as possible. In the two interference conditions, participants see German colour words printed in a different colour (e.g. the written word ‘yellow’ printed in red). In the (iii) reading interference condition, participants must read the word and ignore the colouring. Conversely, in the (iv) naming interference condition, participants must respond to the colouring and ignore the meaning of the word. Reactions in the two interference conditions are usually slower since the processing of the two simultaneously presented stimuli (the written word and the colour in which it is printed) requires attention. This leads to delayed processing and thus to longer reaction times. Each test part consists of 128 stimuli, which are presented until a response is given. Immediately afterwards, the next stimulus appears. The total test duration is approximately 15 min. The ‘naming interference tendency’ is the primary outcome variable. It is calculated from the difference between ‘median of reaction times – naming interference condition’ and ‘median of reaction times – naming baseline’. Using the median reaction time ensures that asymmetries caused by circumstances, such as ‘getting stuck’ on certain items, do not distort results. The reliability of the naming interference tendency measure is α = .97.

**Fig. 2 Fig2:**
[figure not shown]
Illustration of primary outcomes, **a)** the Stroop Interference Test (STROOP) and **b)** the Divided Attention (WAFG). White speakers represent the high-pitched sound. Black speakers depict the low-pitched sound. Squares or speakers outlined in red indicate the targets of the visual and the auditory channels. These targets are either two squares or two high-pitched sounds which immediately follow each other

##### Divided Attention (WAFG)

The WAFG is a measure of cross-modal (visual/auditory) divided attention. In the WAFG, subjects are simultaneously confronted with a visual and an auditory channel (see Fig. 2b). On the former one, either a triangle or a square appears on a computer screen. On the auditory one, either a low- or a high-pitched tone is emitted. The task is to press a key on the response panel as quickly as possible when either two squares or two high-pitched tones immediately follow each other. The total number of items is 85, of which 21 are relevant. Stimuli are presented until a response is given or after a maximum of 1500 ms followed by an inter-stimulus interval of 1000 ms. If no reaction has occurred within the presentation period, an omission error is counted. Reaction times below 100 ms will not be considered, as physiological responses below 100 ms are not possible [50]. The total test duration is 9 min. The outcome variable is the logarithmic mean reaction time, which accounts for the expected skewness in the distribution of reaction times. The WAFG, test form S3, obtains a reliability score of α = .84.

#### Secondary outcomes

Secondary outcomes are cognitive measures of EF other than the STROOP and the WAFG. In particular, we will apply tasks from the three core domains of EF: inhibition, shifting, and updating [30]. For comparison reasons, we will also assess verbal fluency and non-executive components of attention. As these predominantly refer to linguistic and attentional functions, they are less likely to load on EF [51, 52]. Details of the respective tasks for each domain of EF and the corresponding dependent variables are presented in Table 2. Every domain is measured by at least two tasks to better capture each construct [60].

**Table 2 Tab2:** Overview of secondary outcomes

Domain	Task	Test form	Response mode	Description	Dependent variable
Inhibition	INHIB [53]	S3, (go/no-go)	Response panel	A series of circles and triangles is displayed in succession on the screen. Whenever a triangle appears, the subject must press a green button. Circles do not require a response and occur rarely, whereas triangles appear frequently. This builds a dominant response tendency on the triangles. Hence, reactions to circles require inhibition. A total of 250 stimuli are presented, comprising 202 triangles and 48 circles.	Number of commission errors (number of false reactions to circles)
	STROOP [48]	S7	Response panel	The task is described in detail in the primary outcomes section.	Reading interference tendency
Shifting	SWITCH [54]	S1	Response panel	A sequence of triangles and circles appears one by one on the screen. The figures are either dark or light grey. The task is to categorise each stimulus alternately by shape or brightness. After every two stimuli the feature to be attended changes. In case of an incorrect response, the feature to be considered in the next stimulus is displayed (e.g. shape). This hint helps the respondent return to the task after a possible loss of overview. In total, 160 stimuli are presented.	Task switching speed, task switching accuracy
	TMT-B – TMT-A [55]	S2, S4	Touch-screen	This task consists of two parts: A (S2) and B (S4). In part A, numbers from 1 to 25 are randomly displayed on the screen. The task is to connect the numbers in ascending order as quickly as possible. In part B, numbers (1–13) and letters (A – L) are presented. The task is now to alternately link numbers and letters in ascending order (e.g. 1 – A – 2 – B etc.).	Difference score (working time B – A)
Updating	DSB [56]	N/A	Verbal	The test leader is reading a series of numbers aloud. The participants must repeat the numbers in reverse order. The task consists of eight items with a constant increase of one number per item. Each item may be attempted twice. If not at least one sequence of numbers of an item can be repeated correctly, the task stops.	Number of correct trials
	NBV [57]	S1, S3	Response panel	Consonants are displayed one after the other on the screen. If a consonant is identical to the one that has been displayed two places (S1) or three places back (S3), the respondent must react by pressing the green button. S1 contains 100 consonants. In S3, 140 consonants are shown.	Number correct
Verbal fluency	WIWO [58]	S2, S4	Verbal	In these two tasks, the subject must name within two minutes as many words as possible that belong to the category of first names (S2) or begin with the letter K (S4).	Number of correct words
Attention	WAFA [59]	S1	Response panel	Twenty-five black circles are presented one by one on the screen. The task requires to react as quickly as possible by pressing the green button when a circle appears.	Logarithmic mean reaction time
	DSF [56]	N/A	Verbal	The procedure is identical to that of the DSB *(see above)*. The task is to repeat the numbers in the same order.	Number of correct trials
	TMT-A [55]	S2	Touch-screen	*See above.*	Working time

Abbreviations: *DSB* Digit Span Backwards, *DSF* Digit Span Forwards, *INHIB* Response Inhibition; *N/A* Not applicable, *NBV* N-Back Verbal, *STROOP* Stroop Interference Test, *SWITCH* Task Switching, *TMT-A/−B* Trail-Making Test – Langensteinbach Version part A/part B, *WAFA* Perception and Attention Function Battery – Alertness, *WIWO* Vienna Verbal Fluency Test

##### Inhibition

Inhibition is the ability to suppress unwanted reactions. It will be assessed using the Response Inhibition (INHIB) [53] and the ‘reading interference tendency’, which is another outcome measure of the STROOP, as already described in the Primary outcomes section.

##### Shifting

Shifting refers to the ability to switch flexibly between tasks or mental sets. We will measure shifting using the SWITCH [54] and the Trail-Making Test – Langensteinbach Version part B minus part A (TMT-B – TMT-A) [55].

##### Updating

Updating (as a core working memory process) reflects the ability to maintain and continuously update information. It will be evaluated using the Digit Span Backwards (DSB) from the Wechsler Adult Intelligence Scale – Fourth Edition (WAIS-IV) [56] and the N-Back Verbal (NBV) [57].

##### Verbal fluency

Verbal fluency is defined as a person’s ability to find words of a specific characteristic in the mental lexicon [51]. To assess verbal fluency, we will conduct the Vienna Verbal Fluency Test (WIWO) [58]. The test distinguishes between two dimensions: semantic and lexical verbal fluency.

##### Attention

Attention will be represented by a measure of alertness, a basal process of short-term attention activation. It will be measured using the Alertness, a subtest of the Perception and Attention Function Battery (WAFA) [59]. Attention span and information processing speed will be assessed using the Digit Span Forwards (DSF) from the WAIS-IV [56] and the TMT-A [55], respectively.

#### Language course outcomes

We will collect the following language course outcomes to evaluate the intervention:

##### Adherence

Adherence to the language course will be documented daily by the Spanish language teacher. The teacher will inform the study team if a participant does not show up for class without giving prior notice.

##### Homework and learning time

We will collect information about the time spent on additional learning activities in Spanish at home. In a table, participants will indicate in minutes, how much time they invested each day, including at weekends, in doing homework and voluntary learning activities in Spanish. Records will start from the beginning of the course and will end on the last day of the course. The outcome is the total time spent on additional learning activities at home.

##### Course evaluation

A questionnaire will be completed anonymously on the last day of the course to evaluate the perceived quality and acceptability of the intervention. On a four-point Likert scale from ‘fully agree’ to ‘fully disagree’ or ‘cannot judge’, participants will give their opinions on the lessons, the teacher, the textbook, their degree of motivation, and their general satisfaction with the course. Additionally, three open format questions allow participants to provide more specific feedback on aspects they appreciated, disliked, or would recommend for improvement.

##### Vocabulary test

To assess the degree of acquired Spanish language skills, participants will take a vocabulary test on the last day of the course. Following the example of Berggren et al. [22], the vocabulary test will include 108 out of around 577 words learnt during class. Two points will be awarded if the word translated from German into Spanish is translated and spelt correctly. One point will be granted if it has the correct meaning but is misspelt, ignoring punctuation. If the translation is wrong or no answer is given, zero points will be assigned. Thus, a maximum of 216 points can be achieved.

### Participant timeline

Figure 3 illustrates the flow of participants through the trial. Eligibility for participation will be ascertained via a telephone and a subsequent face-to-face screening. In the telephone screening, initial inclusion and exclusion criteria regarding demographic, medical and health-related aspects (see Table 1) as well as availability to participate in the intervention and assessments will be clarified. Moreover, self-reported foreign language skills and usage will be surveyed. Participants who claim to possess few previous skills in Spanish and have not yet attained level A1.1, or who have attended less than one regular course (< 18 h of classes), will be asked a list of questions to determine their Spanish skills. The questions are derived from units 1–5 of the course book [39]. An appointment for the face-to-face screening will be scheduled if they meet all eligibility criteria clarified by telephone.

**Fig. 3 Fig3:**
[figure not shown]
CONSORT flow diagram of participants

The face-to-face screening will take around 2 h and will evaluate the remaining exclusion criteria. The CFD will be applied to exclude participants with suspected cognitive decline and the whispered voice test [37] will be used to ascertain sufficient hearing. Participants who indicated in the telephone screening to already have slight experiences in Spanish will take a placement test [61] to ensure that their previous skills are low enough (< level A1.1) for a Spanish course for beginners. Additionally, further baseline data will be collected (see section ‘Baseline variables’).

Subjects that meet eligibility criteria after the face-to-face screening will be randomly assigned to either the LLG or the WLCG. Within 2 weeks before the start of the language course or the three-week waiting period, both groups will participate in a pre-assessment. Both post- and 3-month follow-up assessments will be carried out within 2 weeks immediately (post) and 3 months (3-month follow-up) after the end of the intervention or the waiting period. After this, the LLG will have completed study participation while the WLCG will attend the control group programme consisting of the language course and a voluntary 4-month follow-up assessment.

Pre-, post-, and follow-up assessments will last around 2 h each and will be scheduled at the same time of day, either in the morning or in the afternoon, to control for day-dependent variability in cognitive performance. Assessments will include both the primary and secondary outcome measures listed in Fig. 1. The test order will be randomised by a computer for each individual. However, the WAFA, as the most straightforward task, will always be applied first to allow participants to become familiar with the computerised test system.

To enhance participant retention, we will arrange appointments for pre-, post-, and follow-up assessments with each participant individually before the start of the study. A confirmation document with the scheduled dates and times will be sent to participants. Additionally, participants will receive reminder phone calls 1 week before each assessment. There will be no financial compensation apart from the language course, which will be offered for free. However, participants may obtain information about their results and the conclusion of the study after having completed participation.

### Sample size

Sample size calculation was based on the main (first) research question for the two primary outcomes, the STROOP and the WAFG, and was conducted using G*Power (version 3.1.9.2). The alpha level was set to α = .05 with the power to detect significant differences of 0.8. A total of *N* = 42 participants will be needed to detect a medium effect size of *d* = 0.25 [24, 26, 62] between pre- and post-assessment, assuming a correlation between repeated measures of *r* = .5. We will adjust for multiple comparisons using the Bonferroni correction. A total sample size of *N* = 60, with *n* = 30 individuals per group, will be required to account for a 30% drop-out rate [24].

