### Statistical analysis

Statistical analysis will be conducted using IBM SPSS Statistics 26 (IBM Corporation: Armonk, NY, USA). We will use the intention-to-treat dataset, considering all participants as randomised who have completed at least pre-assessment and regardless of adherence to protocol. Hypotheses will be tested two-sided on an alpha level of α ≤ .05, which will be adjusted for multiplicity for primary outcomes by applying the Bonferroni correction. Multiple imputation techniques will be applied to account for missing data assuming that data are missing at random (MAR). Additionally, we will report reasons for withdrawal and analyse them qualitatively.

Primary and secondary outcomes will be analysed using 2 (group) × 3 (time) repeated measures analysis of variance (ANOVAs) with group as between-subjects factor and time-point of assessment (pre-, post-, 3-month follow-up) as within-subjects factor. Bonferroni’s post hoc test will be conducted to test hypotheses. We predict a significant group x time interaction, in which the LLG will outperform the WLCG at post- compared to pre-assessment (hypothesis 1) and at 3-month follow-up compared to pre-assessment (hypothesis 2). Partial eta square (*η*_*p*_^2^) will be used as an indicator of effect size.

For the LLG, exploratory subgroup analyses will be performed to evaluate whether effects of foreign language learning on cognitive outcomes are dependent on different levels of cognitive reserve (hypothesis 3) and foreign language knowledge and usage (hypothesis 4). Therefore, we will conduct multiple and simple regression analyses, respectively. The difference in primary outcome measures between pre- and post-assessment will be defined as the dependent variable. Age and indicators of cognitive reserve (CRI-Education, CRI-WorkingActivity, CRI-LeisureTime, and CRI-Index) (hypothesis 3) and the LSBQ-score (hypothesis 4) will be considered as independent variables.

Additionally, we will investigate whether short-term effects of foreign language learning on cognitive measures also apply to the WLCG after completing the control group programme. For this purpose, the WLCG will serve as its control. Using *t*-tests for dependent means, we predict a significant difference between the difference scores from 3- to 4-month follow-up compared to the difference scores from pre- to post-assessment.

To assess the robustness of results, we will perform sensitivity analyses for the following:

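### The sample size paragraph states 80% power for d = 0.25, but N = 42 reproduces only if 0.25 is Cohen's f, most plausibly a 1.0 SD between-group difference in pre-post change

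*Protocol article*

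**What the plan says.** The Sample size section bases the calculation on the first research question and the two primary outcomes, using G*Power. It sets the error rates: "The alpha level was set to α = .05 with the power to detect significant differences of 0.8". For the figure of 42 the wording is: "participants will be needed to detect a medium effect size of *d* = 0.25 [24, 26, 62] between pre- and post-assessment". The pre and post scores are taken to correlate at .5. On multiplicity the section adds: "We will adjust for multiple comparisons using the Bonferroni correction". The total is raised to 60, 30 per group, for 30% drop-out.

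Under Primary outcomes, the Stroop naming interference tendency and the divided attention reaction time "are the two primary outcome measures". The Statistical analysis section tests hypothesis 1 through the group-by-time interaction of a repeated measures ANOVA, post against pre. On alpha it says: "Hypotheses will be tested two-sided on an alpha level of α ≤ .05, which will be adjusted for multiplicity for primary outcomes", by Bonferroni. Cohen's f is not mentioned anywhere in the article.

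**The concern.** By the usual convention 0.25 is a medium value for f, and a medium d is 0.5. The number and the word medium therefore fit f, while the printed symbol is d. This is more than a matter of notation, because the two scales describe very different effects in this design. If the calculation used f, the trial is sized for a difference several times larger than a reader will take from the paragraph. The paragraph is the article's only statement of what the trial can detect. Anyone planning a later study, or weighing the result of this one, would take from it that 42 evaluable participants suffice for a quarter of a standard deviation.

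**Working it through.** **Inputs.** From Sample size: effect size 0.25, power 0.8, alpha .05 with Bonferroni correction, r = .5, drop-out 30%. From Primary outcomes: two primary outcomes, so alpha = .05/2 = .025 each. From Statistical analysis: two-sided tests, group-by-time interaction. From Allocation and blinding: 1:1 allocation. Inferred, not stated: the G*Power test and the number of time points. The words about pre- and post-assessment suggest two.

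**1. Reproduce 42.** For the within-between interaction, with k groups and m time points:

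lambda = f² × N × m / (1 − r), df1 = (k − 1)(m − 1), df2 = (N − k)(m − 1).

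With f = 0.25, k = 2, m = 2, r = .5: lambda = 0.0625 × N × 2 / 0.5 = 0.25N.

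| alpha | N | lambda | power |
|---|---|---|---|
| .025 | 40 | 10.0 | .793 |
| .025 | 42 | 10.5 | .815 |
| .05 | 32 | 8.0 | .781 |
| .05 | 34 | 8.5 | .807 |

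So 42 is the smallest balanced N at alpha .025, and 34 at alpha .05. Drop-out also reproduces: 42 / 0.7 = 60.

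**2. What f = 0.25 means here.** A two-sample comparison of change scores has noncentrality (N/4) × (delta / SD of change)². Setting this equal to 0.25N gives delta = 1.0 SD of change. The SD of change is SD × √(2(1 − r)) = SD × √(2 × 0.5) = 1.0 SD. The detectable effect is therefore a between-group difference in pre-post change of 1.0 outcome SD. As a check, the t-test on change with delta = 1.0, 21 per arm and alpha .025 has noncentrality 1.0 × √(21/2) = 3.24 and power .815, the same figure.

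**3. Does any reading of d = 0.25 give 42?**

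- *Between-group difference in change of 0.25 SD.* With 21 per arm the noncentrality is 0.25 × √(21/2) = 0.81, against a critical value of 2.33 at alpha .025. For 80% power this needs 306 per arm (alpha .025) or 253 per arm (alpha .05).
- *Converted as f = d/2 = 0.125.* This needs N = 156 (alpha .025) or 128 (alpha .05).
- *Paired pre-post effect of 0.25 SD of change.* This needs 155 or 128 participants, two-sided.
- *Difference of 0.25 SD, adjusted for baseline (ANCOVA).* Power at N = 42 is 9% (alpha .025) or 15% (alpha .05).

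Power per primary outcome for the first two readings:

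| Reading of d = 0.25 | alpha | N = 42 | N = 60 |
|---|---|---|---|
| Difference in change | .025 | 7% | 10% |
| Difference in change | .05 | 12% | 16% |
| f = d/2 | .025 | 25% | 36% |
| f = d/2 | .05 | 35% | 48% |

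**4. Is the route to 42 unique?** No. With f = 0.25, three time points and alpha = .05/6, the smallest N is also 42 (power .817). The within-subject main effect of time, with two groups, two time points and alpha .025, uses the same lambda and degrees of freedom and gives 42 as well. Both still need 0.25 to be f.

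**The case against.** The strongest objections concern reach rather than the arithmetic.

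A reader might infer a second contradiction, that the paragraph gives alpha .05 while the calculation used .025. The documents do not support this. Both the Sample size and the Statistical analysis sections state a Bonferroni correction, and two primary outcomes share the .05. That 42 appears at .025 shows the text and the number agreeing on alpha. At most, the per-outcome value could be written out.

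A reader might also take the 7% alone and conclude that a benefit of d = 0.25 would be missed 93 times in 100. That is the lowest value in the range. It needs d to be the between-group difference in change, alpha .025, and only 21 analysed per arm. The plan randomises 60 and analyses everyone with a pre-assessment using multiple imputation, so on that reading power lies between 7% and 10%. The figure is also per outcome. If the two outcomes were independent, which is an assumption, the chance that at least one is significant is 1 − (1 − 0.074)² = 14% at 21 per arm, or 1 − (1 − 0.099)² = 19% at 30 per arm. The wording about pre- and post-assessment could also fit a within-group d.

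The exact G*Power inputs are inferred, and the 1.0 SD equivalence belongs to the two-time-point interaction. This stands, so the sponsor should confirm the inputs.

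Finally, the article states no rule for reading a null result, so a claim that one would be misread is conjecture. Commitments on confidence intervals or null-result wording go beyond correcting the figure. None of these objections rescues d = 0.25 as the effect behind N = 42.

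**Conclusion.** Wrong as written. The claim of 80% power for d = 0.25 with 42 participants cannot be reproduced. The same N follows exactly from f = 0.25. On the most plausible inputs (group-by-time interaction, two time points, r = .5, alpha .025 per outcome) the detectable between-group difference in change is 1.0 SD, four times the printed 0.25 if d is read on that scale. Power for d = 0.25 runs from 7% to 48% depending on how d is defined, which alpha applies and whether 42 or 60 are analysed. The mislabelling is firm, because every route found to 42 needs f. The 1.0 SD figure depends on the inferred test and number of time points, and on the stated r = .5. The error is in the stated detectable effect. The sample size, the design and the analysis are not shown to be wrong by this point.

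**What to change.** In the Sample size section, replace d = 0.25 with f = 0.25. Have the sponsor confirm from the G*Power record the test chosen, the number of time points, and the per-outcome alpha of .025 that the stated Bonferroni correction implies. Then state the implied detectable difference in pre-post change, which is 1.0 SD for the interaction with two time points at r = .5, in place of the claim of 80% power for d = 0.25. If the confirmed inputs differ, the implied difference should be recalculated from them.

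The cost is wording only. N stays at 42 evaluable and 60 randomised, which matters because 54 participants were already enrolled at submission. The stated detectable effect becomes less favourable.
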